### Procedures

After interested participants contact the research assistant and are determined to be eligible to participate in the study, (and provide an approximate date for contact 2 months post-baby) we schedule a fitness test at our lab. At the initial visit to the lab, signed informed consent is obtained from participants by the project coordinator after overviewing the requirements of the study. Participants are assigned an identification number and all data is attached to this number to ensure confidentiality. A qualified exercise professional is employed to ensure consistency of the fitness testing procedures [68] and is also present at the first initial meeting. This individual is responsible for quality control throughout the fitness-testing portion of the trial. The fitness testers are blind to the treatment conditions of the participants. Both parents are given accelerometers to wear for 1 week and instructed on how to enter information about each day’s activity in a log. Fitness testers provide a short training session on how to wear and use the accelerometers. After the 1 week wear of accelerometers, participants are randomized at a 1:1 ratio to either intervention or control group, using an online randomizer program. Participants as well as the research assistants and project coordinator are aware of the group allocations, but all fitness testers are blinded to treatment allocation. The project coordinator and research assistants have to be aware of the condition to which participants are randomized in order to deliver the appropriate materials. The project coordinator and research assistant meet with participants at their home or location of choice to go through their specific intervention materials. Two people attend the house visits for safety reasons.

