After the initial 6 week intervention period, couples are given online follow-up questionnaires sent via email to complete and accelerometers are dropped off to their house to be worn for another week and then are picked up by the research assistant. Contact is made initially with a phone call by the research assistant to setup a meeting time with participants and to prime them for the emailed online questionnaire. Both groups receive a site “booster” session on the same material but the intervention group focuses on revisiting their experiences over the past six-weeks and re-set goals and redefine/problem-solve obstacles. Participants in the control group receive a booster session but this is more of a general check in. The same protocol is followed at the 3 month time period. Thus, two booster sessions (six-weeks, 3 months) are provided to all participants. At 6 months follow-up (i.e., 8 months post-baby), parents are asked to return to the lab to complete a brief questionnaire, perform the final fitness test and participate in a brief end-of-trial quantitative questionnaire and qualitative interview to evaluate the impact of the intervention and usefulness of the intervention material. To gain a better understanding of the factors associated with physical activity we conduct semi-structured interviews with parents, in order to examine both *content fidelity* (“what is done”) and *process fidelity* (“how it is done”) related to the delivery of the intervention trial [18]. Although quantitative measurement of outcomes will enable us to examine the potency of our intervention, a process evaluation (whereby participants are interviewed) is also essential to examine the *extent to which the* program is delivered and implemented as planned.

To help study retention, we offer monetary compensation in the form of grocery store gift cards ($25 per participant, increasing by $5 each assessment) across the study.

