##### Musculoskeletal fitness

Grip strength, push ups, sit & reach flexibility, partial curl-ups, vertical jump, and back extension will be measured to determine the musculoskeletal fitness of both the children and parents using the procedures established by Gledhill and Jamnik [25] Change in musculoskeletal fitness from baseline to 6 months (i.e., post-intervention) will be examined.

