### Analysis strategy

Missing data will be evaluated for patterns of missingness for each psychosocial variable and behavior at all time points using the dummy coding procedures of Allison [2]. Depending on the outcome of these tests (e.g., missing at random, missing completely at random, etc.) we will initiate the appropriate missing data handling strategy. Intention to treat analyses will also be performed in addition to sensitivity analysis procedures. An assessment of covariates will also be performed. As one would expect during early parenthood many factors may contribute to inactivity which include but are not limited to child care status, leave status, baseline quality of life and other general demographics. The RCT approach aids in some equalization in the group x time effect of these factors, yet it is acknowledged that some of these confounds may affect the time effect regardless of randomisation.

To address the first objective, hierarchical linear modeling will be used in HLM 6.0. First, a Level-1 no intercept model will be specified such that a main effect will be entered for father (0 = Mother; 1 = Father), Mother (0 = Father; 1 = Mother), a Father linear trend (0 = baseline; 1 = 6 months), and a Mother linear trend with all coefficients set to random. In this model, the main effects for the fathers and mothers’ intercepts represent their respective baseline minutes of MVPA, whereas the linear trends represent the change in MVPA (or not) over the 6-month interval. At Level-2, cross-level interactions will be added such that condition (0 = control; 1 = intervention) predicts the fathers’ Level-1 intercept / slope and the mothers’ Level-1 intercept / slope. These potential interactions will determine whether baseline MVPA is similar between conditions and whether the potential change in MVPA across time is similar between conditions accounting for the couple variation. Second, the fathers vs. mothers’ coefficients will be statistically compared using the multivariate hypothesis testing procedure (e.g., to determine if the magnitude of change in the minutes of MVPA is the same for fathers and mothers). Third, the correlations among the fathers and mothers’ intercepts and slopes will be examined to determine, for example, whether the mothers’ baseline minutes of MVPA are significantly associated with their own change in MVPA and / or their fathers’ change in MVPA (and vice versa).

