To address the second and third objectives / hypotheses concerning the motivational, health-related quality of life, and health-related fitness outcomes, the same analytical approach as outlined in relation to objective 1 will be used when examining the variables as outcomes. However, to examine whether the Theory of Planned Behavior (TPB) variables explain the potential MVPA differences between conditions (i.e., whether the TPB variables mediate the condition/MVPA relationship), the appropriate Level-1 mediation analysis approach [32, 33] will be used treating the TPB variables as time varying covariates [60] while accounting for the couple variation. Finally, the fourth objective / hypothesis (i.e., whether season, gender) potentially moderate the condition / outcome relationships) will be examined by including the time invariant covariates (e.g., gender) at level-2 of the hierarchical model (i.e., by creating cross-level interactions to predict the fathers/wives’ intercepts and slopes at Level-1) and the time varying covariates (e.g., motivation variables, season) at Level-1 of the model. The primary investigator and project coordinator will have access to the final trial data set.

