### Justification of sample size

It is recognized that two analytical approaches can be utilized in longitudinal couple studies within hierarchical linear modeling. First, a 3-level model can be created where repeated assessments (Level-1) are nested within the individual (Level-2) that are nested within the couple (Level-3) [4]. However, we have chosen to utilize the more common approach, which is to nest the individual repeated assessments (Level-1) within the couple (Level-2) ([4]; S. [43]). Therefore, we used the OpDes Program for power estimation of hierarchical linear models (S. W. [44]) to calculate the sample size needed for our analyses. Specifically, with a frequency of 4 measurement occasions, a duration of 6 months, within-person variance of 1.0, a growth rate of 1.0, and a moderate effect size (.40), a total of 200 couples (i.e., 100 couples per condition) are needed to show a significant adherence to MVPA as measured via accelerometry. The effect size represents the low-end of findings from prior intervention research with this demographic [17, 21, 22, 34, 38], yet it is clearly in the clinically meaningful range (D.E.R. [65]). These studies showed mean increases of moderate to vigorous physical activity of 80 min per week, which is over half of the recommended weekly activity for public health [62]. Our sample size includes a potential 25% attrition rate similar to the longitudinal study (thus total recruitment *N* = 267. The attrition in the prior trial was actually 15% [48], but we sought to oversample to accommodate the active component of this experimental trial compared to the prior passive prospective design. Our over-sampling procedures account for attrition due to second pregnancy or other possible reasons for drop out such as break-up, moving away, etc. The prediction-based research will be examined by group condition as well as via the collapsed sample for mediation analyses. Considering an average of five predictor IVs (TPB model), and using a small-medium effect size (f^2^ = .10) we will have sufficient power (.80) to evaluate these predictors at an alpha of .05. Our longitudinal study also supported the use of a small-medium effect size as an appropriate criterion [47]. Finally, the evaluation of physiological outcomes of participants across time will follow a 2 (condition) × 2 (time) interaction. The proposed sample size is, therefore, more than adequate to ensure sufficient statistical power for the physiological measurements.

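### Fitness is measured at two visits only, so the four-random-coefficient model assigned to it has one covariance parameter too many, and its intercept/slope correlations cannot be estimated

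*Protocol article*

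**What the plan says.** **Visit schedule for fitness.** In Procedures, eligible couples start with a lab visit ("we schedule a fitness test at our lab"), and at 6 months they return to "perform the final fitness test". After the first 6 weeks, "couples are given online follow-up questionnaires sent via email to complete and accelerometers are dropped off to their house"; the same steps are followed at 3 months, and neither contact includes a fitness test. The Musculoskeletal fitness section agrees: "Change in musculoskeletal fitness from baseline to 6 months (i.e., post-intervention) will be examined".

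**Model.** The Analysis strategy defines the objective-1 model without a common intercept. It has a father term, a mother term, "a Father linear trend (0 = baseline; 1 = 6 months") and "a Mother linear trend with all coefficients set to random". Condition predicts each parent's intercept and slope at the couple level. A third step examines the correlations among the parents' intercepts and slopes. For the motivational, quality-of-life and fitness outcomes, "the same analytical approach as outlined in relation to objective 1 will be used when examining the variables as outcomes".

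**Sample-size section.** Justification of sample size nests the repeated records within the couple and lists a within-person variance among its inputs, so the framework includes a residual. It closes by saying that "the evaluation of physiological outcomes of participants across time will follow a 2 (condition) × 2 (time) interaction".

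**The concern.** A random slope for each parent needs more than two time points if it is to be told apart from residual variation. At two visits, a parent's departure from the group mean change may be a true difference in slope or measurement noise, and the data cannot say which. The plan carries the four-visit model to fitness by name and makes no exception for outcomes measured twice.

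Two things are at stake. First, the third analysis step, applied to fitness, would yield correlations whose values depend on an arbitrary split of variance. Second, the plan leaves open which model replaces the one that cannot be fully estimated, and the sample-size section describes the fitness analysis in other terms without linking the two.

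**Working it through.** The plan states no figure for the fitness model, so there is none to reproduce. Its recruitment total, 200 / (1 − 0.25) = 267 couples, is reproduced but has no bearing on this point.

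**Inputs**
- Fitness occasions: 2, coded 0 and 1 (Procedures, Musculoskeletal fitness, Analysis strategy).
- Parents per couple: 2, with the couple as the upper level (Justification of sample size).
- Random coefficients: 4, all free to covary (Analysis strategy; the third step needs the covariances).
- Residual variance: 1.

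**Counting**
- Random-effect variances and covariances: 4 × 5 / 2 = 10. Adding the residual gives 11 parameters.
- Fitness: 2 × 2 = 4 records per couple, so 4 × 5 / 2 = 10 distinct moments. The derivative matrix of the moments with respect to the 11 parameters has rank 10, so the model is not identified.
- Physical activity at four visits: 2 × 4 = 8 records, so 8 × 9 / 2 = 36 moments. The rank is 11 for 11 parameters, so the model is identified.

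**What is lost.** Write the couple's covariance as V = Z T Z′ + σ²I, where T is the random-effect covariance. At two visits Z is 4 × 4 and invertible, so T = Z⁻¹(V − σ²I)Z⁻¹′. Every admissible σ² gives a T with exactly the same V. For each parent:
- intercept variance = Var(baseline) − σ²;
- slope variance = Var(change) − 2σ²;
- intercept–slope covariance = Cov(baseline, change) + σ².

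The covariances between the two parents do not involve σ². The correlations therefore shift with a quantity about which the data carry no information, however many couples are enrolled.

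**Illustration.** One data set of 200 couples was simulated from an invented covariance matrix:

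| Residual variance imposed | Log-likelihood | Father–mother slope correlation | Mothers' intercept–slope correlation |
|---|---|---|---|
| 0.01 | −1146.61 | 0.20 | −0.39 |
| 0.1 | −1146.61 | 0.25 | −0.36 |
| 0.2 | −1146.61 | 0.32 | −0.31 |
| 0.3 | −1146.61 | 0.46 | −0.24 |

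**What survives.** The 8 fixed effects (two intercepts, two slopes and the effect of condition on each) have rank 8. In the same data the condition-by-time estimates and their standard errors were identical in all four rows.

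**Identified alternatives.** Dropping the separate residual leaves 10 parameters with rank 10, which is an unstructured 4 × 4 covariance. Keeping only the two intercepts random leaves 4 parameters with rank 4.

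**Precision.** With complete data at two visits, the effect of condition on slope is a comparison of mean change. If the variances at the two visits are equal and the baseline-to-6-month correlation is ρ, then

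variance with baseline adjustment / variance of change = (1 − ρ²) / [2(1 − ρ)] = (1 + ρ) / 2.

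At ρ = 0.8 this is 0.90 (10% lower); at ρ = 0.5 it is 0.75 (25% lower). The document gives no value of ρ, so both are assumptions. The gain is the same against the objective-1 slope contrast and against a 2 × 2 interaction, since both estimate the difference in change.

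**The case against.** The strongest reply is that little of consequence is lost. The model exceeds what the data can support by exactly one parameter, the covariance of the four records is fully determined, and the treatment contrast with its standard error is unaffected. That stands. A reader might infer that the fitness treatment effect cannot be estimated or that the model will fail outright. The algebra does not support the first, and the documents do not show how the software would behave.

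A reader might also infer that the plan names two conflicting methods. The documents do not show this. With time coded 0 and 1, condition acting on slope is the condition-by-time interaction for each parent, and the sample-size sentence names no separate estimator. That sentence also shows that the authors knew fitness had two occasions. What remains is that the two sections are not tied together, and the 2 × 2 sentence does not say how the couple enters.

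Nor does it follow that the model would have to be changed after the data are seen. The respecification depends only on the visit schedule and can be made now.

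Finally, one sentence in an article may condense detail that belongs in an analysis plan. That would answer a complaint of missing detail. Here the article fixes the random effects and extends them by name to an outcome whose stated schedule cannot support them.

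**Conclusion.** The point holds for the variance components of the fitness outcomes: 11 covariance parameters against 10 moments, with the intercept/slope correlations not estimable. This rests on the stated two-visit schedule, on all four coefficients being random and free to covary, and on a residual being present.

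It does not reach the fitness treatment contrast or the primary physical activity outcome. It does not reach the motivational outcomes either if they are collected at all four visits, as the follow-up questionnaires suggest. The schedule for quality of life is not given, so nothing is concluded there.

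The precision gain of 10% to 25% is a reason to prefer one remedy over another and is not evidence of the fault. It depends on the assumed correlations and on equal variances. The matter concerns secondary outcomes and is worth correcting because the correction is cheap.

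**What to change.** In the Analysis strategy, keep the objective-1 model for outcomes measured at all four visits and add a separate statement for outcomes measured only at baseline and 6 months:

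- **Preferred:** model the 6-month value of both parents together, with parent, condition, parent × condition and own baseline value as fixed terms and an unstructured 2 × 2 mother–father residual covariance. The baseline fitness test precedes randomisation, so it is a proper covariate and is already collected.
- **Also identified:** an unstructured 4 × 4 covariance for the four records with no separate residual, which keeps the planned change contrast.

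State that intercept/slope correlations will not be reported for these outcomes from the four-random-coefficient model. State the visit schedule for quality of life so that it falls clearly under one model. Align the 2 × 2 sentence in Justification of sample size with the model chosen.

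The cost is a few sentences. No extra data are needed, and the change can be made without looking at any outcome.

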### Justification of sample size

It is recognized that two analytical approaches can be utilized in longitudinal couple studies within hierarchical linear modeling. First, a 3-level model can be created where repeated assessments (Level-1) are nested within the individual (Level-2) that are nested within the couple (Level-3) [4]. However, we have chosen to utilize the more common approach, which is to nest the individual repeated assessments (Level-1) within the couple (Level-2) ([4]; S. [43]). Therefore, we used the OpDes Program for power estimation of hierarchical linear models (S. W. [44]) to calculate the sample size needed for our analyses. Specifically, with a frequency of 4 measurement occasions, a duration of 6 months, within-person variance of 1.0, a growth rate of 1.0, and a moderate effect size (.40), a total of 200 couples (i.e., 100 couples per condition) are needed to show a significant adherence to MVPA as measured via accelerometry. The effect size represents the low-end of findings from prior intervention research with this demographic [17, 21, 22, 34, 38], yet it is clearly in the clinically meaningful range (D.E.R. [65]). These studies showed mean increases of moderate to vigorous physical activity of 80 min per week, which is over half of the recommended weekly activity for public health [62]. Our sample size includes a potential 25% attrition rate similar to the longitudinal study (thus total recruitment *N* = 267. The attrition in the prior trial was actually 15% [48], but we sought to oversample to accommodate the active component of this experimental trial compared to the prior passive prospective design. Our over-sampling procedures account for attrition due to second pregnancy or other possible reasons for drop out such as break-up, moving away, etc. The prediction-based research will be examined by group condition as well as via the collapsed sample for mediation analyses. Considering an average of five predictor IVs (TPB model), and using a small-medium effect size (f^2^ = .10) we will have sufficient power (.80) to evaluate these predictors at an alpha of .05. Our longitudinal study also supported the use of a small-medium effect size as an appropriate criterion [47]. Finally, the evaluation of physiological outcomes of participants across time will follow a 2 (condition) × 2 (time) interaction. The proposed sample size is, therefore, more than adequate to ensure sufficient statistical power for the physiological measurements.

## Results

The study is on-going with recruitment wrapping up in late 2017. Ethical approval was obtained, and the trial was registered with a government clinical trials database. The study has followed the Standard Protocol Items: Recommendations for Intervention Trials (SPIRIT) [14, 15] and the full checklist can be found in Additional file 3. To date a total of 152 couples have been recruited with 88 couples who have completed all four measures. Sixteen couples have dropped out after baseline testing due to a variety of reasons including not enough time, moving, and post-partum depression. Remaining participants are expected to wrap up all measures by early 2018. Please see Fig. 1 for the participant flow chart [14, 15].

**Fig. 1 Fig1:**
[figure not shown]
Participant Flow Diagram

## Discussion

This protocol describes the implementation of a randomized controlled trial that utilizes motivational and self-regulation strategies to try and maintain and/or increase physical activity among new parents. Research findings could be useful in public health in providing effective strategies to new parents to help prevent the decline in physical activity that often accompanies having a newborn. Additionally, findings may help to inform future interventions aimed at increasing physical activity among new parents as well as informing public health materials for new parents. Findings from this trial will be disseminated in peer-reviewed journals and presented at academic conferences.
